# 3. TRIAL STRUCTURE

## 3.1 Study Population

Patients presenting to a TB clinic clinically suspected pulmonary TB.

## 3.2 Entry Criteria

### ***Inclusion criteria***

Patients with newly diagnosed pulmonary tuberculosis (with or without pleural effusion) will be admitted to the study provided they fulfil the following criteria:

- two sputum specimens positive for tubercle bacilli on direct smear microscopy. A patient is considered smear positive if: (i) 2 out of 3 consecutive sputum smears are read as positive, or (ii) 2 out of 5 are read as positive in the event that only one of the first three smears is positive, in which case the patient will be asked for two more specimens: one morning and one spot.
- no history of previous anti-tuberculosis chemotherapy, or antiretroviral therapy.
- aged 18 years and over
- a firm home address and intent to remain there during the entire treatment and follow up period
- informed consent to participate in the study.
- weight between 40.00 kg and 70.00 kg inclusive.
- acceptance of HIV counselling and testing
- CD4 ≥ 220 cells/microlitre blood if the patient is HIV positive in Nigeria
- CD4 > 350cells/microlitre blood if the patient is HIV positive In Ethiopia

### ***Exclusion criteria***

- Positive urinary pregnancy test or obviously pregnant on physical examination
- additional extrapulmonary TB (e.g. bone, meningeal, peritoneal or miliary)
- contraindications to any medications in the study regimens (e.g. documented allergy; optic neuritis, blurred vision, red-green colour blindness and poor visual acuity ; any active hepatic diseases.
- evidence (laboratory and/or clinical history) of pre-existing non-tuberculous disease likely to affect the response to, or assessment of, treatment: (i) diabetes mellitus, (ii) liver impairment, (iii) renal impairment, (iv) peripheral neuropathy, (v) terminal illness such as with malignancy.
- requirement for hospitalisation for any reason other than directly observed treatment (DOT)
- concomitant immunosuppressive treatment during the whole study period.
- psychiatric illness, alcohol or drug abuse likely to lead to uncooperative behaviour
- patients on antiretroviral treatment during TB treatment period.

***Study withdrawals***

- AFB smear positive patients found later to be culture negative. These patients will be withdrawn from the study but they will be assessed clinically to see if treatment should be continued or not. (This occurs in 1-5 % of newly diagnosed cases).
- Patients withdrawing consent in the course of the trial
- Antiretroviral therapy initiation within the first six months of anti-TB medication.
- AFB smear positive patients at week 20 whose sputum culture and DST confirm resistant to isoniazid and rifampicin (MDR TB)
- Drug toxicity necessitating interruption of treatment

Patients who withdraw from study or are lost to follow up will however still be included in the intention to treat (ITT) analyses set.

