# 2. RATIONALE AND OBJECTIVES

# 2.1 Rationale

Owing to the length (6-8 months) and complexity (4 drugs, up to 16 tablets a day) of the current treatment, the delivery of short-course chemotherapy for TB with single drug formulations is challenging and poses risks of prescription errors and lack of compliance with treatment where DOTS is either poorly or not used. Drug supply management is complicated, since individual drugs must frequently be ordered from different sources, and there is a risk of out-of-stock situations, in which patients may be treated with too few drugs, or even only one drug in isolation. Another major concern in the treatment of tuberculosis is to prevent the emergence of drug resistance especially to isoniazid and rifampicin, the two most potent antitubercular drugs.

One approach to tackling these challenges is to use fixed dose combinations (FDCs) of the four and two TB drugs that are used in the intensive and maintenance phases, respectively. However, these drugs have been little used to date despite being recommended by the WHO and the IUATLD. One concern is the variable bioavailability of rifampicin in poor quality fixed dose combinations. Some rifampicin containing FDCs with adequate absorption in healthy normal volunteers have been endorsed by the WHO.6Poor absorption may occur in HIV infected individuals.

The advantages of FDCs over loose drugs could include the following:

- The emergence of HIV/AIDS has complicated treatment of TB among co- infected patients (HIV-infected TB cases). The increasing availability of HAART (highly active antiretroviral therapy) in the public sector in resource-limited settings and the increasing mortality among HIV-infected TB cases managed alone with TB drugs implies the need for concomitant treatment of HIV and TB. 4FDCs presents a rational approach to managing the huge burden that would otherwise ensue in these categories of patients, which could lead to drug resistance from dropping off some TB medications in loose formulations.

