- Due to the enormous costs involved in treating drug-resistant tuberculosis, preventing the emergence of drug resistance must be given the highest priority. Mitchison argues that multiple interruptions of treatment regimes are considered the predominant cause of drug resistance TB13. When using single-drug formulations, due to the length (6-8 months) and complexity (four drugs, up to 16 tablets per day) of the treatment patients are more prone to continue their treatment with one drug while interrupting the others, thus it creates a risk of mono-therapy and selection of drug resistant mutants. Hence a clinical trial should be conducted to address such issues.
- In the past, some researchers claimed that adverse reactions to 3FDCs are not more common than loose combination anti-TB. To date, no data is available on the safety and adverse reactions associated with 4FDCs.

In conclusion, if their potential is realized, the 4FDCs and 2FDCs can be a means of improving TB control but FDCs have not been assessed adequately in countries like Ethiopia and Nigeria where HIV seropositivity among TB patients is high. Therefore, there is a need to increase the evidence base on which to recommend FDCs in TB control programme and other settings.

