### ***Primary Outcome measures***

- cure rates at end of treatment (6 months). A cure is defined as one negative sputum culture in patients who did not fail treatment. A treatment failure is defined as:

1. a patient who is persistently smear positive by five months of treatment
2. a patient who becomes smear negative but positive again at or after five months of treatment (note: sputum positivity before this time is not considered a treatment failure)

- ***Secondary outcome measures***
- early response rates: proportion of patients with negative culture results at 8 weeks after initiation of therapy
- proportion of patients with relapses during the 72 weeks follow up period after the end of treatment. A relapse is a patient previously treated for tuberculosis who has met the case definition of cure (as defined above) and been declared cured by a physician and who has now been diagnosed with bacteriologically positive (two positive smears and culture positive) tuberculosis. If there is discordance between smear and culture results, a clinical decision will be made regarding further management: (i) smear positive, culture negative, and (ii) smear negative and culture positive.
- cure rates in HIV positive TB patients
- proportion of patients with clinical deterioration of pulmonary tuberculosis with the need for hospitalisation
- proportion of patients with *serious* adverse events any time during chemotherapy
- proportion of patients with any adverse events during chemotherapy
- proportion of patients completing treatment (defined as patients who achieved a total of 54 out of 56 doses in the first eight weeks of treatment AND 107 out of 112 doses at a daily rate during the subsequent 16 weeks of treatment) within each group. (96% doses taken considered as completed in intensive and maintenance phases).
- Proportion of patients who developed MDR-TB

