## 3.4 Treatment Regimens

### ***Study drugs:***

The drug regimens (see tables) will consist of 8 weeks of daily directly observed treatment (DOT) treatment, followed by 16 weeks of daily directly observed treatment. There will be two arms: (i) the intervention group - treatment will consist of 4FDCs (8weeks, i.e. **56 doses**) and 2FDCs (16 weeks, i.e. **112 doses**), and (ii) the comparator group - treatment with the same four and two drugs administered as loose formulations. The 4FDCs and the 2FDCs used will be identical across the different study sites, Nigeria and Ethiopia. Both 4FDCs and 2FDC preparations will include rifampicin. Full details of the drug regimen, including drug dosages, for each patient and of the procedure to be followed are given on the front and back of each Treatment Card.

The doses of drugs to be given to each patient are shown below and are based on the weight of the patient at the time of starting treatment.

*2. Weight between 40-54 kg (inclusive)*

*Intensive phase*.

For the patients allocated to the intervention regimen (FDCs) the dose for the first eight weeks of treatment is shown in the table below:

| MEDICATION  Combined tablet (COMB) of: | WEIGHT IN KILOGRAMMES |
| --- | --- |
|  | 40-54 |
| Ethambutol (275mg)  Rifampicin (150mg) Isoniazid (75mg) and  Pyrazinamide(400mg) | 3 tablets |

For patients allocated to the comparator regimen, the dose for the first eight weeks of treatment is shown in the table below:

| MEDICATION | WEIGHT IN KILOGRAMMES |
| --- | --- |
| as loose tablets (SEPA) | 40-54 |
| Ethambutol (400mg)  Rifampicin (450 mg)  Isoniazid (225mg)  Pyrazinamide (400 mg) | 2 tablets  1 tablet  1 tablet  3 tablets |

*Maintenance phase*.

For the maintenance phase, drugs will be administered under daily observation. The doses shown in the table below are based on the weight of the patient upon completion of the initial intensive phase:

| MEDICATION  Combined tablet (COMB) of: | WEIGHT IN KILOGRAMMES |
| --- | --- |
|  | 40-54 |
| Rifampicin (150mg)/Isoniazid (75mg) | 3 tablets |

For the comparator group, the regimen is shown below:

| MEDICATION  as loose tablets (SEPA) | WEIGHT IN KILOGRAMMES |
| --- | --- |
|  | 40-54 |
| Rifampicin (150 mg)  Isoniazid (225 mg) | 3 tablets  1 tablet |

*2. Weight between 55-70 kg (inclusive)*

*Intensive phase*.

For the patients allocated to the intervention regimen (FDCs) the dose for the first eight weeks of treatment is shown in the table below:

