## 3.5 Treatment Allocation

Patients are to be allocated to the different treatment arms according to a computer generated randomisation list. The randomisation list will be prepared and kept by the Study Director. Each centre will be provided with a batch of sealed envelopes. The total number of allocated envelopes will correspond to their expected intake to the study. Therefore, each patient will be allocated randomly **either** the FDCs regimen **or** the separate drug regimen. Each sealed envelope will contain a sequential patient code (randomisation number) and a Treatment Card printed with the details of one of the two regimens to which the patient will be allocated. Only a specially assigned person will open the envelope and dispense the drugs to the patient. No other study personnel will be present at the time of drug allocation. This information will, therefore, only be known to the assigned dispenser and the patient. Randomisation is considered to have taken place once the envelope containing the code for the drug regimen is opened. Once a patient is allocated a randomisation number must not be used for other patients, in the event that the patient decides to withdraw voluntary consent before study drug administration. A treatment allocation log will be kept by the specially assigned person and will not be available to the investigators until the analysis has been concluded, or unless the patient’s physician requires this information for safety reasons.

The PI and the clinicians will remain blinded to the drug regimens of individual patients throughout the study.

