## 6.4 Data analysis

The database file generated thus will be converted into statistical package STATA software version 7 (STATA Corporation, Texas, USA) and analysed by the study statistician, and PI in collaboration with the study director. Analysis will be both (a) by intention-to-treat, and (b) per protocol (excluding those who did not receive adequate chemotherapy or were withdrawn from the study), including survival analysis.Subjects will be compared based on their assigned treatment using chi-square, Student's t-test or the Wilcoxon rank sum test as appropriate depending on the scale of measurement and the validity of underlying assumptions for the baseline characteristics. Primary and secondary outcomes for each study subject will be recorded as positive (desirable) and negative (not desirable) at a pre-specified time. For primary outcome Chi-square will be used to compare proportions of culture positive and culture negative subjects at the end of the study in the two treatment groups. The effects of confounding variables (such as age and sex) will be adjusted using multiple logistic regression. In model construction, backward elimination will be employed using important independent variables initially. An alpha of 0.10 will set the significance level for entering a variable into the model. Chi-square will also be used to compare differences in each of the three secondary end points. In the whole analysis, an alpha of 0.05 will set the significance level for testing the null hypothesis. In presenting results exact p-value as obtained from the computer program will be presented.

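### The toxicity withdrawal rule does not say whether holding one drug counts, so it is open to unequal use by arm, and the patients it removes have no stated route to the culture that defines cure

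*Protocol*

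**What the plan says.** The list of study withdrawals in Protocol section 3.2 includes "Drug toxicity necessitating interruption of treatment". It does not say whether this means one drug or the whole regimen, or a brief or a lasting stop. The same list ends by keeping withdrawn patients in the intention-to-treat (ITT) set.

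Section 3.4 sets out the contrast. In the intervention arm, "treatment will consist of 4FDCs (8weeks, i.e. 56 doses) and 2FDCs (16 weeks, i.e. 112 doses"; the comparator is "treatment with the same four and two drugs administered as loose formulations". In the intensive phase the loose regimen is 2 + 1 + 1 + 3 = 7 tablets a day in four products at 40-54 kg, and 3 + 1 + 1 + 3 + 4 = 12 tablets in five products at 55-70 kg. The intervention arm takes 3 or 4 identical tablets, each holding all four drugs.

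Section 2.2 defines cure by a negative sputum culture in a patient who has not failed treatment. Section 3.6 schedules that culture at week 24 but does not say that a withdrawn patient will have it. Section 6.4 plans two analyses, by ITT and "per protocol (excluding those who did not receive adequate chemotherapy or were withdrawn from the study".

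**The concern.** In most trials an undefined interruption would be loose drafting. Here it falls on the randomised contrast, because tablet format is what is being compared. A single component can be left out of the loose regimen; it cannot be left out of the combined tablet. The protocol itself recognises that loose drugs can be dropped one at a time, though as an adherence problem: section 2.1 speaks of HAART co-treatment, "which could lead to drug resistance from dropping off some TB medications in loose formulations", and says that on single-drug formulations "patients are more prone to continue their treatment with one drug while interrupting the others".

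If a site does not read a single-drug hold as an interruption, the same reaction could withdraw an FDC patient and leave a control patient in the trial. Both analyses would then depend partly on tablet format:

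- ITT keeps the withdrawn patient but may have no week-24 culture to classify.
- Per protocol loses the patient altogether.

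The margin is 4 points around an assumed 96% cure rate, so a few patients classified differently by arm matter.

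**Working it through.** **1. The passages side by side**

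| Question | What the protocol says |
| --- | --- |
| Is the withdrawal rule worded differently by arm? | No, one wording for both (3.2) |
| Does holding one drug count as interruption? | Not stated |
| Can one component be held? | Loose arm: physically yes. FDC arm: no (tables in 3.4) |
| May an FDC patient move to loose drugs and stay in? | Not stated |
| Does a withdrawn patient have the week-24 culture? | Not stated (3.2, 3.6) |
| Withdrawn patient in ITT? | Kept (3.2); how the outcome is scored is not stated |
| Withdrawn patient in per protocol? | Excluded (6.4) |

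**2. The plan's own sample size.** Inputs from section 4: 96% cure, margin 4 points, one-sided 5%, 90% power, 10% dropout. I take 96% as the true rate in both arms. For a non-inferiority test with the null variance restricted to the margin (Farrington-Manning), the restricted proportions are 0.932 and 0.972, and

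n = [1.645 × √(0.932 × 0.068 + 0.972 × 0.028) + 1.282 × √(2 × 0.96 × 0.04)]² / 0.04² = [1.645 × 0.301 + 1.282 × 0.277]² / 0.0016 ≈ 452 per arm.

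452 × 1.10 = 497.2, rounded up to 498, the stated figure.

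**3. Illustration for ITT.** Assumptions, none of them stated in the protocol:

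- A fraction w of FDC patients is withdrawn for toxicity beyond the control rate.
- Withdrawn patients are scored not cured.
- Control patients with the same reactions stay in and are cured at 96%.

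Then FDC cure = 0.96 × (1 − w), and the apparent difference is d = 0.96w. With n per arm,

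SE = √{[0.96 × 0.04 + p(1 − p)] / n}, where p = 0.96(1 − w)

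chance of meeting the margin = Φ[(0.04 − d)/SE − 1.645].

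For w = 1% and n = 498: p = 0.9504, d = 0.0096, SE = 0.0131, so Φ(0.0304/0.0131 − 1.645) = Φ(0.675) = 75%.

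| Excess FDC withdrawal (assumed) | d, points | 498 per arm | 448 per arm (498 less 10%) |
| --- | --- | --- | --- |
| 0% | 0 | 94% | 92% |
| 0.5% | 0.48 | 87% | 83% |
| 1% | 0.96 | 75% | 71% |
| 2% | 1.92 | 45% | 42% |
| 3% | 2.88 | 19% | 18% |
| 4% | 3.84 | 6% | 6% |

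The 0% row exceeds the planned 90% because this simpler unpooled variance needs only 412 per arm. A 1% excess is 0.01 × 498 ≈ 5 patients.

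**4. Per protocol.** No figure can be derived. If the FDC patients removed would have done worse than average, the FDC cure rate rises; if better, it falls. Control patients with a drug held may or may not be removed too.

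**The case against.** The strongest answer is that the rule is one sentence for both arms. Since comparator treatment is defined as the same four and then two drugs, stopping one of them can fairly be read as an interruption, and the control patient is then withdrawn as well. A reader might infer that the rule does work differently by arm and that a control patient with one drug held stays in. No passage says so. What stands against the rule is that it does not settle the question.

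A reader might also infer that such control patients necessarily remain in both analysis sets. The documents do not support this either: per protocol also excludes patients without adequate chemotherapy, which could remove them without a withdrawal. In the maintenance phase, 16 of the 24 weeks, only two drugs are given. Holding one leaves a single drug, which section 2.1 warns against, so unequal use is least plausible there.

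Two further inferences should be resisted. One is that handling toxicity must break the blind improperly: section 3.5 says "The PI and the clinicians will remain blinded to the drug regimens of individual patients throughout the study", but also releases the allocation to the patient's physician when safety requires it. The other is that a loose-arm day with one drug left out would count towards completion, defined through "patients who achieved a total of 54 out of 56 doses in the first eight weeks of treatment". The dose tables in section 3.4 most naturally make a dose the full set of tablets, and doses are given under observation.

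It is also fair to say that being unable to withhold one component is a real property of a fixed-dose product, which an ITT comparison may legitimately capture. That is a reason to observe these patients' outcomes, not to leave them unobserved. Finally, scoring of withdrawn patients may be set in the analysis plan, which is not at hand. A plan written later cannot, however, supply cultures that were never taken.

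**Conclusion.** The point holds in a limited form. The protocol leaves its toxicity withdrawal trigger undefined where the two arms differ physically, ties that trigger to leaving the study, and then needs these patients for ITT without saying that their defining culture will be taken. The rule is open to unequal use; the documents do not show that it would be used unequally.

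The figures are illustrative only. They rest on an assumed excess withdrawal rate, on scoring withdrawn patients as not cured, and on control patients with the same reactions being retained and cured at the usual rate. If single-drug holds are treated as interruptions in the loose arm too, the excess shrinks, possibly to nothing. The table shows how little excess would matter, not how much to expect. The change is worth making because it is cheap and has to be made before data collection.

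**What to change.** - Separate two things that the list now merges: a toxicity-related change of treatment, and withdrawal from the study.
- Keep every patient with such a change, in both arms, in follow-up with the scheduled week-24 smear and culture, unless the patient withdraws consent.
- Record any toxicity-related change to any component drug as one event category, defined identically in both arms, and report it by arm.
- State one per-protocol rule for that category and apply it to both arms.

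How a reaction is managed stays with the physician; no stopping rule is proposed. The cost is a wording change to section 3.2, a matching sentence in section 6.4, an entry in the case record form, and some extra follow-up and recording for the patients concerned.

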## 3.3 Trial Design

This is a two-arm single-blinded, randomised comparison of 4FDCs (intervention group) versus standard treatment with separate TB drugs (comparator group).

The investigators and laboratory personnel and those responsible for data analysis will be blinded to the allocated treatment regimen. Blinding will occur by separating treatment dispensation from clinical management and from the compilation of laboratory results. Investigators will not be blinded to HIV status as this would be essential for adequate patient management.

## 3.4 Treatment Regimens

### ***Study drugs:***

The drug regimens (see tables) will consist of 8 weeks of daily directly observed treatment (DOT) treatment, followed by 16 weeks of daily directly observed treatment. There will be two arms: (i) the intervention group - treatment will consist of 4FDCs (8weeks, i.e. **56 doses**) and 2FDCs (16 weeks, i.e. **112 doses**), and (ii) the comparator group - treatment with the same four and two drugs administered as loose formulations. The 4FDCs and the 2FDCs used will be identical across the different study sites, Nigeria and Ethiopia. Both 4FDCs and 2FDC preparations will include rifampicin. Full details of the drug regimen, including drug dosages, for each patient and of the procedure to be followed are given on the front and back of each Treatment Card.

The doses of drugs to be given to each patient are shown below and are based on the weight of the patient at the time of starting treatment.

*2. Weight between 40-54 kg (inclusive)*

*Intensive phase*.

For the patients allocated to the intervention regimen (FDCs) the dose for the first eight weeks of treatment is shown in the table below:

| MEDICATION  Combined tablet (COMB) of: | WEIGHT IN KILOGRAMMES |
| --- | --- |
|  | 40-54 |
| Ethambutol (275mg)  Rifampicin (150mg) Isoniazid (75mg) and  Pyrazinamide(400mg) | 3 tablets |

For patients allocated to the comparator regimen, the dose for the first eight weeks of treatment is shown in the table below:

| MEDICATION | WEIGHT IN KILOGRAMMES |
| --- | --- |
| as loose tablets (SEPA) | 40-54 |
| Ethambutol (400mg)  Rifampicin (450 mg)  Isoniazid (225mg)  Pyrazinamide (400 mg) | 2 tablets  1 tablet  1 tablet  3 tablets |

*Maintenance phase*.

For the maintenance phase, drugs will be administered under daily observation. The doses shown in the table below are based on the weight of the patient upon completion of the initial intensive phase:

| MEDICATION  Combined tablet (COMB) of: | WEIGHT IN KILOGRAMMES |
| --- | --- |
|  | 40-54 |
| Rifampicin (150mg)/Isoniazid (75mg) | 3 tablets |

For the comparator group, the regimen is shown below:

| MEDICATION  as loose tablets (SEPA) | WEIGHT IN KILOGRAMMES |
| --- | --- |
|  | 40-54 |
| Rifampicin (150 mg)  Isoniazid (225 mg) | 3 tablets  1 tablet |

*2. Weight between 55-70 kg (inclusive)*

*Intensive phase*.

For the patients allocated to the intervention regimen (FDCs) the dose for the first eight weeks of treatment is shown in the table below:

| MEDICATION  Combined tablet (COMB) of: | WEIGHT IN KILOGRAMMES |
| --- | --- |
|  | 55-70 |
| Ethambutol (275mg)  Rifampicin (150mg) Isoniazid (75mg) and  Pyrazinamide(400mg) | 4 tablets |

For patients allocated to the comparator regimen, the dose for the first eight weeks of treatment is shown in the table below:

| MEDICATION | WEIGHT IN KILOGRAMMES |
| --- | --- |
| as loose tablets (SEPA) | 55-70 |
| Ethambutol (400mg)  Rifampicin (450 mg)  Rifampicin (150 mg)  Isoniazid (100 mg)  Pyrazinamide (400 mg) | 3 tablets  1 tablet  1 tablet  3 tablets  4 tablets |

*Maintenance phase*.

For the maintenance phase, drugs will be administered under daily observation. The doses shown in the table below are based on the weight of the patient upon completion of the initial intensive phase:

| MEDICATION  Combined tablet (COMB) of: | WEIGHT IN KILOGRAMMES |
| --- | --- |
|  | 55-70 |
| Rifampicin (150mg)/Isoniazid (75mg) | 4 tablets |

For the comparator group, the regimen is shown below:

| MEDICATION  as loose tablets (SEPA) | WEIGHT IN KILOGRAMMES |
| --- | --- |
|  | 55-70 |
| Rifampicin (150 mg)  Isoniazid (100 mg) | 4 tablet  3 tablet |

WHO will ensure that the drug preparations are all from the same source. The manufacturer of the drugs is Lupin Pharmaceuticals**.** Bioavailability data on the RH and 4 FDC (RHZE) formulations manufactured by Lupin will be available to the study team through TDR. This includes sufficient information concerning the quality of the product, bioavailability, dissolution testing etc. to pass review by the national regulatory agency for permission to carry out the investigations.

